### Other data collection

The following data will be collected at baseline: gender, date of birth, ethnicity, diagnosis, young person’s email and mobile phone number, and one parent’s contact number and email (Additional file 8). We will record the standard transition care which the young person has received. Established transition services in our patient population includes ACI Transition Care Service, Trapeze Transition Service [25, 26] and joint paediatric and adult clinics. The NSW Health Agency for Clinical Innovation (ACI) Transition Care Service is a state-wide care coordination service responsible for supporting young people (aged between 14 and 25 years) with chronic illness/disability as they move from children’s health services to adult health services. Trapeze is part of the Transition Care Network and provides a supported transition into adult care for patients aged 14–25 within the Sydney Children Hospital Network. We will also obtain the details of the adult service that the treating paediatric team has referred the young person to. Included in the consent is collection of EMR data on measures of illness control and frequency of visits to the paediatric service in the previous 12 months.

Table 1 shows a sample list of conditions and relevant illness markers compiled in consultation with on the Clinical Services which have agreed to take part in the study. If other conditions not mentioned here are included, the research team will determine the preferred control marker in consultation with the respective clinical team.

**Table 1 Tab1:** Sample list of illness markers for chronic illnesses

Chronic illness	Illness marker
Acquired brain injury	Functional Independence Measure (FIM), the Glasgow Outcome Scale (GOS), and the Disability Rating Scale (DRS)
Autoimmune thyroid disease	Free T4; Free T3; TSH
Congenital Adrenal Hyperplasia	17 OHP; Plasma Renin Ratio; Testosterone, Androstenedione, Dehydroepiandrosterone sulfate (DHEAS)
Cystic fibrosis	FEV_1_; Weight
Duchenne muscular dystrophy	Creatinine kinase; Lung function test; GMFCS
Epilepsy	Number and frequency of seizures
Inflammatory bowel disease - Crohn’s, Ulcerative colitis	Weight; CRP; Faecal Calprotectin; ESR
Diabetes (Type 1 and 2)	HbA1c
Chronic liver disease, including Glycogen storage disorders and Transplant	Liver function tests and albumin level
Phenylketonuria	Serum Phe and tyrosine levels
Systemic lupus erythematosus	Antinuclear antibodies
Congenital heart disease and rhythm disorders	Exercise stress test; Echocardiography; ECG

Baseline readiness to transition will be assessed using the Trapeze Transition Readiness Checklist (which is designed by the Trapeze transition service (Available on Trapeze website at http://www.trapeze.org.au/content/checklist-young-people and attached in Additional file 2). The Trapeze Transition Readiness Checklist has not been validated, and to the the best of our knowledge, neither have any of the commonly used transition readiness questionnaires have been fully validated. A score of greater than 37 in the Trapeze Transition Readiness Checklist represents achievement of 70% task competency and would be defined as being “Transition Ready” by expert clinicians in practice.

Mental health risk factors will be assessed at baseline using the validated Kessler Psychological Distress scale (K-10) (Additional file 3). A K-10 score greater than 20 would be considered indicative of having mental health risk factors (possible mental disorder).

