#### Engagement and retention with adult service

Successful engagement with the adult service at 6 months will be defined as confirmed attendance at least one appointment with the adult service by six months post discharge from paediatric care (i.e. after the last paediatric appointment). This will be considered as a *successful transfer* to adult services. This number is chosen because most chronic conditions have guidelines on the optimal number of specialist visits per year with a frequency varying from 3 to 6 months. Routine annual visits are less likely and will be recorded as such.

*Engagement* with the adult service will be assessed, with consent of the young person/parent, (provided at enrolment) via phone call to the young person and nominated adult service at 6 months post discharge from paediatric care. If the young person has not attended the service they were referred to, they will be asked if they are attending an alternate service and for consent to contact this service. Young people who cannot be contacted at 6 and 12 months post discharge from the paediatric service will be considered to have unsuccessful engagement and be a *failed transfer* to adult care.

*Retention* within the adult service will be defined as at least one confirmed attendance with the adult service in the preceding 6 months at 12 and 18 months follow up. These data will be collected, with consent, via phone call to the young person and the adult service to obtain information regarding attendance at the adult service at 12 and 18 months follow up. Young people who cannot be followed up at 12 and 18 months post discharge from the paediatric service will be considered to not be retained by the adult service (*failed retention*).

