### Outcomes

#### Primary outcome

To measure engagement with adult services, we will review attendance of the participants at adult appointments at 6 months. Engagement is defined by at least one attendance to the adult service in the preceding 6 months at the 6 months follow-up. This is obtained from the adult service or patient self-report via study-specific questionnaires. (Questionnaires in Additional files) and will be supplemented by information from hospital databases. TMApp analytics will provide further information on the TMApp usage.

Time point: At 6 months after last clinic appointment at paediatric service.

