### Participant timeline

**Table Taba:** 

**Example procedures**	**Assessment/ Procedure**	**Initial Assessment (*Penultimate or Final Paediatric appointment**	**6 months**	**12 months**	**18 months**
	**Informed Consent** **(Additional file** **1****)**	**x**			
	**Demographic Information including standard transition care received** **Including information about Adult Service referred to** **(Additional file** **8****)**	**x**			
	**Measure of disease control**	**x**	**x**	**x**	**x**
	**Transition Readiness Assessment Questionnaire** **(Additional file** **2****)**	**x**			
	**Kessler Psychological Distress Scale (K-10)** **(Additional file** **3****)**	**x**			
	**Download and use TransitionMate app**	**x**	**x**	**x**	
	**Phone call or text message to young person re: attendance/engagement with adult service and measure of disease control** **(Additional files** **4****,** **5****,** **6****)**		**x**	**x**	**x**
	**Phone call or written request to adult service re: attendance/engagement with adult service and measure of disease control** **(Additional files** **4****,** **5****,** **6****)**		**x**	**x**	**x**
	**Semi-structured interview (face-face, Skype or Telephone) about effectiveness of TransitionMate app** **(Additional file** **4****)**			**x**	

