### Methods in analysis to handle protocol non-adherence and any statistical methods to handle missing data

Handling of non-adherence is not called for other than recording non-adherence data as an outcome.

Missing data will be managed as recording only. If data are missing and remain missing from any time point of collection the assumption will be that this represents non-engagement with the adult service.

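### The adult service used to check attendance is scheduled to be recorded once, at enrolment, so an attender at another service who is not reached can be scored as a failure

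*Protocol article*

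**What the plan says.** **Recording the service.** Under Other data collection: "We will also obtain the details of the adult service that the treating paediatric team has referred the young person to". That sentence carries no date. In the Participant timeline the item appears inside the demographics row as "Including information about Adult Service referred to" and is ticked in the first column only, headed "Penultimate or Final Paediatric appointment". The Inclusion criteria admit patients due to transfer at any time in the following 12 months.

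**Using it.** Under Engagement and retention with adult service, attendance is checked "via phone call to the young person and nominated adult service at 6 months post discharge from paediatric care". The one correction described is: "If the young person has not attended the service they were referred to, they will be asked if they are attending an alternate service". Consent to contact that other service is then sought from the young person.

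**Scoring.** In the same section: "Young people who cannot be contacted at 6 and 12 months post discharge from the paediatric service will be considered to have unsuccessful engagement". A parallel rule covers retention at 12 and 18 months. The missing-data section adds that for data that stay missing "the assumption will be that this represents non-engagement with the adult service". Under Measures of illness control, a participant whose markers cannot be had from the adult service counts as deteriorated.

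**Sources.** Under Primary outcome: "This is obtained from the adult service or patient self-report via study-specific questionnaires". Hospital databases are named as a supplement.

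**The concern.** The entry that directs the adult-service check is made before the last paediatric visit for anyone enrolled earlier than that visit. The referral can be changed or completed afterwards, and no step is described that looks at it again from the paediatric side. A young person who answers the phone can put the record right. One who does not answer cannot, and for that person the adult service is the main remaining source.

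If the service on file is not the one attended, it will truthfully report no attendance. A true attender then becomes a failure for engagement or retention, and the marker request goes to a clinic that holds no results, which the illness-control rule turns into a deterioration. On this route errors go only from success to failure. They lower a rate that has to clear 70%, and they would tend to be more frequent in participants enrolled earlier.

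**Working it through.** **1. Age of the entry.** Upper bound: 12 months to transfer + 6 months = 18 months at the primary outcome, then 24 and 30 months at the later follow-ups. For enrolment at the penultimate visit, with visits 3 to 6 months apart (the interval the article gives for specialist care), it is 3 + 6 = 9 to 6 + 6 = 12 months. For enrolment at the final visit it is 6 months, with no paediatric visit in between.

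**2. When a wrong entry changes the primary outcome.** Each row is a participant who truly attended an adult service by 6 months.

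| Young person | Service on file | If an adult-service reply can count alone | If non-contact alone means failure |
|---|---|---|---|
| Reached | Right | Engaged | Engaged |
| Reached | Wrong | Corrected by asking | Corrected by asking |
| Not reached | Right | Engaged | Failed |
| Not reached | Wrong | Failed, unless a hospital database shows the visit | Failed |

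The entry matters only in the last two rows of the third column. The Primary outcome section supports that column, because it allows either source. The contact rule under Engagement and retention, read literally, supports the fourth. The deterioration rule turns on whether the adult service supplies markers, not on contact, so there a wrong entry matters on both readings.

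**3. The plan's figures.** 49 / (1 - 0.30) = 70, as stated. The rule is that the lower limit of the 90% exact interval must exceed 70%. At n = 49 this needs 40 successes (lower limit 0.701), and 80% power is reached at a true rate of 84.8%. The article states no alternative rate, so 85% is used below as an assumption. Missing outcomes count as failures, so all 70 stay in the denominator. At n = 70 the rule needs 56 successes (lower limit 0.705; 55 gives 0.689).

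**4. Illustration.** Let u be the proportion not reached and w the proportion of unreached attenders at a service other than the one on file, with no database recovery. Attendance is taken as equal in reached and unreached participants, and an adult-service reply can count alone.

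Observed rate = 0.85 × (1 - u × w). Chance of passing = P(X ≥ 56) for a binomial with n = 70 at that rate.

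| w | u = 0.30: rate | Chance | u = 0.10: rate | Chance |
|---|---|---|---|---|
| 0 | 85.0% | 0.906 | 85.0% | 0.906 |
| 0.10 | 82.5% | 0.762 | 84.2% | 0.866 |
| 0.20 | 79.9% | 0.563 | 83.3% | 0.818 |
| 0.30 | 77.4% | 0.358 | 82.5% | 0.762 |

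The 0.30 for u reuses the stated attrition as phone non-contact. The 0.10 for u and every value of w are assumed.

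**5. The literal contact rule.** If non-contact alone means failure, u = 0.30 gives 0.85 × 0.70 = 59.5% and a chance of about 0, whatever service is on file.

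**The case against.** **The contact rule makes the entry irrelevant.** Read literally, it fails anyone not contactable at 6 and 12 months, with no exception where the adult service confirms attendance. This stands for engagement, and for retention under its parallel rule. A better entry helps those outcomes only if the rule is also clarified. It does not answer the deterioration outcome.

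**There are other safeguards.** Each time point has up to five calls plus a text message, the engagement rule names two time points, and hospital databases supplement the outcome. These reduce the problem. The article does not say which hospitals' databases are meant, and its Discussion notes that participants disperse to many centres, so recovery is possible but not assured.

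**Twelve months is the extreme.** This is so. Recruitment aims at the penultimate visit, the timeline also allows the final one, and the referral is described as already made. The gap will often be shorter.

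**An article condenses.** The tick sits in a merged row of a timeline that is labelled as examples, and the full protocol may contain a re-check. That limits the weight of the point. Still, the schedule does state a timing, and no other section gives a later one.

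**Stronger readings to avoid.** A reader might infer that an outdated entry is never corrected. It is, for those who are reached. A reader might also put the loss at 3 to 8 percentage points (0.30 × 0.5 × 0.2 = 3.0 to 0.30 × 0.7 × 0.4 = 8.4). The documents give neither the share of unreached participants who attend nor the share with a wrong entry. With half of the unreached attending and 85% overall, attendance among those reached would have to be (0.85 - 0.30 × 0.5) / 0.70 = 100%, so the lower part of that range cannot be paired with a plausible 85%.

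**Conclusion.** The point holds in a limited form. The schedule shown fixes the adult service at enrolment, and the only described update depends on reaching the young person. A true attender at another service who is not reached can be scored as not engaged or not retained, provided that an adult-service reply would otherwise have counted and no database recovers the visit. The same participant can be scored as deteriorated on either reading of the contact rule. The bias is one-way, against the app.

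Its size is unknown. The illustration runs from a small effect (0.906 to 0.866 with 10% not reached and 10% of unreached attenders elsewhere) to a large one (0.906 to 0.358 with 30% and 30%). It rests on an assumed true rate of 85%, equal attendance in reached and unreached participants, and assumed rates of changed service. It shows sensitivity and is not an estimate. The documents do not support the inference that the outdated entry is the decisive cause of false failures, because the literal contact rule would do more harm by itself.

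**What to change.** 1. In Other data collection and the Participant timeline, add a step after the last paediatric appointment: confirm or update the adult service from the paediatric record or the treating team. Use that entry for the 6-, 12- and 18-month contacts unless the participant names an alternate service, which then takes precedence.
2. In Engagement and retention with adult service, state that attendance confirmed by the adult service or a hospital database counts as engagement or retention even when the young person is not reached. This brings the contact rule into line with the Primary outcome section. Without it, the first change does not help engagement or retention for unreached participants.

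The cost is one look-up per participant, with no extra visit and no extra recruitment. One check is needed first: the consent described for record access names illness-control measures and visit frequency, and contact with an alternate service is sought from the participant at the time. The investigators should confirm that enrolment consent covers the referral details and contact with an updated service. The change does not help an unreached participant who chose a service that the paediatric team does not know of.

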#### Engagement and retention with adult service

Successful engagement with the adult service at 6 months will be defined as confirmed attendance at least one appointment with the adult service by six months post discharge from paediatric care (i.e. after the last paediatric appointment). This will be considered as a *successful transfer* to adult services. This number is chosen because most chronic conditions have guidelines on the optimal number of specialist visits per year with a frequency varying from 3 to 6 months. Routine annual visits are less likely and will be recorded as such.

*Engagement* with the adult service will be assessed, with consent of the young person/parent, (provided at enrolment) via phone call to the young person and nominated adult service at 6 months post discharge from paediatric care. If the young person has not attended the service they were referred to, they will be asked if they are attending an alternate service and for consent to contact this service. Young people who cannot be contacted at 6 and 12 months post discharge from the paediatric service will be considered to have unsuccessful engagement and be a *failed transfer* to adult care.

*Retention* within the adult service will be defined as at least one confirmed attendance with the adult service in the preceding 6 months at 12 and 18 months follow up. These data will be collected, with consent, via phone call to the young person and the adult service to obtain information regarding attendance at the adult service at 12 and 18 months follow up. Young people who cannot be followed up at 12 and 18 months post discharge from the paediatric service will be considered to not be retained by the adult service (*failed retention*).

#### Feedback about the TMApp

Participants will complete a semi-structured interview with a member of the research team (in person or via Skype or teleconference) at the end of the 12 month follow up period to provide feedback about ease of use, frequency and barriers in regard to the use of the TMApp (See Additional file 4).

Analytics (digital footprint) of participants’ interaction with the app will be also obtained. These analytics are de-identified, grouped data that will document how often the app is used, the frequency and duration of use of the app, time spent on the app and the most frequently used functions. There is a disclaimer for the TMApp on both the App store and Google play store to ensure only study participants download the application.

### Criteria for discontinuing or modifying allocated interventions

The intervention may be subject to modification in the following circumstances: to ensure optimal functioning of the TMApp (to address crashes; fix bugs; necessary updates as required by the application operating systems – Android and IOS) and if there are significant issues identified by the participant or the research team during the study.

### Strategies to improve adherence to interventions

A fortnightly reminder message (“Any events coming up?” “Time to check your TO DO list”) is incorporated into the TMApp to encourage engagement of the participants with the app. The messages are sent at 7 pm every other Sunday through the TMApp. This time was chosen as the day that the young people are least likely to have after-hours commitments.

### Relevant concomitant care permitted or prohibited during the trial

The Transition Mate application is in addition to and does not preclude the participants from any existing transition support and services.

### Outcomes

#### Primary outcome

To measure engagement with adult services, we will review attendance of the participants at adult appointments at 6 months. Engagement is defined by at least one attendance to the adult service in the preceding 6 months at the 6 months follow-up. This is obtained from the adult service or patient self-report via study-specific questionnaires. (Questionnaires in Additional files) and will be supplemented by information from hospital databases. TMApp analytics will provide further information on the TMApp usage.

Time point: At 6 months after last clinic appointment at paediatric service.

#### Secondary outcomes

To measure retention, we will review attendance of the participants at adult appointments at 12 and 18 months. Retention is defined by at least one further attendance to the adult service in the preceding 6 months at the 12 and 18 months follow-up. This is obtained from the adult service or patient self-report via study-specific questionnaires. (Questionnaires in Additional files 4, 5, 6) and will be supplemented by information from hospital databases.To understand change in illness control during the first 18 months post transition, we will review the changes in the markers of illness control from baseline. We will also assess the number of unplanned/ emergency hospital admissions of the participants after their last paediatric appointment. These are obtained from the adult service or patient self-report via study-specific questionnaires. (Questionnaires in Additional files 4, 5, 6) and will be supplemented by information from hospital databases.To understand if the use of the TMApp can assist with preventing deterioration of chronic illness control in young people in the 12 months post transition, we will analyse the changes in illness control with TMApp usage data. This will be obtained from TMApp analytics as well as adult service or patient self-report via study-specific questionnaires. (Questionnaires in Additional files 4, 5, 6) which will be supplemented by information from hospital databases.

Time point: At 6 months, 12 months (primary endpoint) and 18 months after last clinic appointment at the paediatric service.

### Participant timeline

**Table Taba:** 

**Example procedures**	**Assessment/ Procedure**	**Initial Assessment (*Penultimate or Final Paediatric appointment**	**6 months**	**12 months**	**18 months**
	**Informed Consent** **(Additional file** **1****)**	**x**			
	**Demographic Information including standard transition care received** **Including information about Adult Service referred to** **(Additional file** **8****)**	**x**			
	**Measure of disease control**	**x**	**x**	**x**	**x**
	**Transition Readiness Assessment Questionnaire** **(Additional file** **2****)**	**x**			
	**Kessler Psychological Distress Scale (K-10)** **(Additional file** **3****)**	**x**			
	**Download and use TransitionMate app**	**x**	**x**	**x**	
	**Phone call or text message to young person re: attendance/engagement with adult service and measure of disease control** **(Additional files** **4****,** **5****,** **6****)**		**x**	**x**	**x**
	**Phone call or written request to adult service re: attendance/engagement with adult service and measure of disease control** **(Additional files** **4****,** **5****,** **6****)**		**x**	**x**	**x**
	**Semi-structured interview (face-face, Skype or Telephone) about effectiveness of TransitionMate app** **(Additional file** **4****)**			**x**	

